### Data collection

Prior to data collection, all participants regardless of study arm (laboratory or real-world) will complete a questionnaire to provide information pertaining to their demographics, lifetime athletic injury history, medical history, sporting pursuits and running personal bests (S1 Appendix). Injury will be classified as “any muscle, bone, tendon or ligament pain in the lower back/legs/knee/foot/ankle that caused a restriction or stoppage of running (distance, speed, duration or training) for at least 7 days or 3 consecutive scheduled training sessions, or that required the runner to consult a physician or other health professional” [31–33].

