### Data processing

All collected data will be anonymised, stored, and saved in the main computer, password protected. Data processing will be performed in Vicon Nexus. All markers will be labelled, and marker trajectories were filtered using a fourth order low-pass Butterworth filter via dynamic plug-in gait model with 6 Hz cut-off frequency. Gait identification will be achieved through visual inspection of foot strike and toe off for consecutive strides over the 60s. A threshold of 20 N in ground reaction force will used to determine initial contact and toe-off. Kinetic variables will be normalized using base factors of gravitational constant g (9.81 m/s^2^), leg length, L (m), and body mass, M (kg).

Wearable device data (DANU Sport and DorsaVi ViMove2) will be processed as per the manufacturer’s guidelines, whereas the Axivity AX6 data processing will be carried out from the nine axis (accelerometer, magnetometer, and gyroscope) raw signal by a previously validated in-house algorithm [47]. A master data table will be created with all available outcomes, categorised by subject and date, including a column to indicate distinguishing factors (e.g., those with previous injury history, different performance levels).

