To examine the analytical (concurrent) validation of running gait outcomes measured in real-world settings from the various grades of wearables in all real-world testing participants (n = 40), we will compare outcomes across the wearable devices (research, commercial and novel multi-modal) through widely used measures of agreement. The absolute difference, r, ICC, the level of agreement through the Bland Altman plots, 95% LoA, RMSEs will be calculated to evaluate agreement between outcomes generated by each wearable [48].

*Exploratory clinical validation analysis*. To provide an initial exploration of clinical (performance) validation, we will investigate group difference and relationships with clinically (or performance) relevant measures. For group differences (e.g., previous injury history or performance level), analysis of co-variance (ANCOVA), will be conducted to assess for differences between groups (injured vs non-injured, or elite vs novice) in the individual running gait outcomes (e.g., ground contact time etc.) from the novel multimodal, commercial and research-grade wearable devices during the running tasks, while controlling for demographics that are significantly related to the running gait outcomes. Relationships between running gait outcomes and demographic variables (e.g., sex, age, height, weight etc.) within groups (injured vs non-injured, or elite vs novice) will be completed through Pearson correlations within each grade of wearable device (research, commercial, multimodal).

To examine the usability of the wearable devices the SUS scores for each wearable will be calculated and visualised. To investigate differences in participant perception of the usability for each grade of wearable, separate analysis of variance (ANOVA) tests will be performed. The ANOVAs will determine the differences between the SUS scores within the different device grades between participant groups (e.g., injury history, performance level). The relationships between the SUS scores, demographics (e.g., sex, age, age-grade performance), and wearables characteristics (e.g., price, weight, and battery life) will be explored using Pearson correlations [39]. The strength of the correlation will be assessed based on Cohen’s criteria: correlations < 0.30 are considered small, correlations between 0.30 and 0.50 will be considered medium, and correlations > 0.50 are considered strong [53].

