### Exploratory clinical validation

Following the examination of analytical validity and reliability the protocol will seek to examine runners in a more natural running environment to provide initial evidence on clinical (or performance) validity (i.e., do the analytically valid outcomes provide something meaningful). By moving beyond the laboratory to more natural running environments (i.e., indoor, or outdoor running tracks, or sports venues), we will be able to evaluate whether the different grades of wearables (research-grade, commercial, novel multimodal) acceptably measure and provide meaningful insight in the specified context of use [23]. This study will determine what grade of wearable may be necessary to provide meaningful data on real-world running. The use of sub-group analyses will elucidate outcomes that are most representative of an individual’s running gait, as well as reveal the interactions between confounding demographic factors, injury status and performance level aid performance enhancement and reduce injury risk / occurrence [59–61]. The proposed protocol will allow for examination of such factors and hopes to provide clarity for researchers and practitioners on the applicability of certain wearables in context.

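### The exploratory ANCOVAs do not adjust the performance contrast for injury history, and adjust the injury contrast for performance at most conditionally, although both factors are recorded for every runner.

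*Protocol article*

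**What the plan says.** All references are to the Protocol article.

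- **Contrasts.** Under Statistical analysis (Exploratory clinical validation analysis), ANCOVA is used for "differences between groups (injured vs non-injured, or elite vs novice"). These are two separate contrasts, and no model containing both factors is described.
- **Covariates.** The models are fitted "while controlling for demographics that are significantly related to the running gait outcomes". For the gait correlations in the same paragraph the examples are "demographic variables (e.g., sex, age, height, weight etc".), an open list. For the usability correlations in the next paragraph the list is "demographics (e.g., sex, age, age-grade performance").
- **Groups.** Laboratory testing recruits 20 runners with and 20 without previous lower limb injury. Real-World environment testing recruits 20 novice/amateur and 20 expert/sub-elite runners, classified by age-graded 5 km performance. Neither section mentions matching or balancing on the other factor.
- **Data held.** Data collection states that "all participants regardless of study arm (laboratory or real-world) will complete a questionnaire", which covers "lifetime athletic injury history, medical history, sporting pursuits and running personal bests". Data processing describes a master table "including a column to indicate distinguishing factors (e.g., those with previous injury history, different performance levels").
- **Stated aim.** The Discussion (Exploratory clinical validation) says that the sub-group analyses will reveal interactions between "confounding demographic factors, injury status and performance level".

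**The concern.** The groups are not randomised, and each set is formed on a single characteristic. If previously injured laboratory runners are on average faster or slower than the others, and gait varies with ability, part of the injury contrast is a performance contrast. The same holds the other way round in the field if more of one performance group has been injured. The covariate rule is written for demographics, so it does not deal reliably with either case.

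Real-World environment testing frames clinical and performance validity as whether the devices can tell relevant populations apart. Crediting a difference to the wrong population characteristic bears directly on that aim. The Discussion also promises a joint look at the factors that the analysis section does not supply.

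**Working it through.** **1. The plan's own figure.** Sample size calculation gives 20 per group by rule of thumb, with no effect size, SD or power, so it cannot be reproduced. For orientation, at two-sided 5% (two-sidedness is an assumption), the difference detectable with 80% power is (1.960 + 0.842) × √(2/20) = 0.886 SD, or about 0.91 SD with the t distribution. Power at 0.5 SD is about 0.35.

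**2. What can enter each model.**

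| Contrast | Other factor | Route into the ANCOVA |
|---|---|---|
| Field: elite vs novice | Injury history | None on any reading |
| Laboratory: injured vs non-injured | Age-graded performance | Not named; possible only if treated as a demographic and significant |

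**3. Laboratory contrast, continuous other factor.** Assumptions: 20 vs 20; no true injury effect; groups differ by Δ SD in age-graded performance; gait correlates ρ with it. The false difference is Δ × ρ. Rejection follows from the noncentral t with 38 df and noncentrality Δρ × √(20/2).

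| Δ | ρ | False difference (SD) | Noncentrality | Rejection, unadjusted |
|---|---|---|---|---|
| 0.3 | 0.3 | 0.09 | 0.285 | 5.9% |
| 0.5 | 0.5 | 0.25 | 0.791 | 12.0% |
| 0.8 | 0.5 | 0.40 | 1.265 | 23.4% |

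Simulation agrees, giving 23.6% in the last row. With the covariate always included, bias is about 0.00 and rejection about 5%. At Δ = 0.5 and ρ = 0.5 the mean standard error falls from about 0.314 to about 0.285.

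**4. Entry only if significant.** With 40 runners, the power to flag a covariate is 0.23, 0.47, 0.73 and 0.92 at correlations of 0.2, 0.3, 0.4 and 0.5 (Fisher z). At Δ = 0.5 and ρ = 0.3 the covariate is selected in about half of studies. The mean remaining bias is 0.045 SD, against 0.5 × 0.3 = 0.15 SD with no adjustment, and rejection is close to 5%.

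**5. Yes/no other factor, as injury history would be in the field contrast.** Assumptions: the factor shifts gait by d SD; 20 vs 20; no true group effect; 20,000 simulated studies per row. The false difference is d × (difference in proportions). Variance inflation from adjusting is 1/(1 − φ²), where φ is the correlation between the two factors. For these splits φ equals the difference in proportions; for 14/20 vs 6/20, 1/(1 − 0.4²) = 1.19.

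| Split on other factor | False difference, d = 0.5 to 1.0 | Rejection, unadjusted | Variance inflation |
|---|---|---|---|
| 10/20 vs 10/20 | 0.00 | 4.5% to 2.7% | 1.00 |
| 12/20 vs 8/20 | 0.10 to 0.20 | 5.4% to 6.1% | 1.04 |
| 13/20 vs 7/20 | 0.15 to 0.30 | 6.5% to 10.8% | 1.10 |
| 14/20 vs 6/20 | 0.20 to 0.40 | 8.6% to 17.4% | 1.19 |
| 16/20 vs 4/20 | 0.30 to 0.60 | 14.0% to 40.4% | 1.56 |

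Rejection is 4.6-5.2% in every row when the factor is always included, and 4.9-6.2% when it enters only if significant. The second option is not open to injury history under the rule as written.

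**The case against.** A reader might infer that neither factor can ever enter the other's model. For the laboratory contrast that goes too far. The usability paragraph counts age-grade performance as a demographic and the gait list is open, so performance may be eligible. If it is, most of the inflation disappears (step 4). This stands, and it limits the laboratory half of the point to an unnamed and conditional adjustment.

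A reader might also infer that the groups are in fact unbalanced, or that injury history and performance are known to be related. The documents say neither. They give group sizes and one grouping factor, and no stated matching is not evidence of imbalance. The upper figures need a large imbalance and a strong correlation together.

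The fixed treadmill speeds (8, 10, 12 and 14 km/h) limit whatever part of a performance effect acts through speed. They do not help the overground runs at self-selected speed, or the fifth treadmill speed, which is set from the 5 km personal best.

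The work is labelled exploratory, Sample size calculation leaves control of relevant variables to future research, and an unadjusted known-groups contrast answers a legitimate question. That is a reason to keep the unadjusted result, but not to omit the adjusted one when the data are already held. Finally, adjustment is not free: it costs precision when the factors overlap, and the other factor may lie on the pathway, so the adjusted estimate is not automatically the right one.

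**Conclusion.** The point holds in a limited form. Injury history is left out of the field performance model on every reading. Performance is not named for the laboratory injury model and enters at most conditionally. If the groups happen to differ on the other factor, a difference may be credited to the wrong characteristic.

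The size depends wholly on assumptions. It runs from no bias under balance, through 0.25 SD and 12% rejection in the middle laboratory case, to 0.40 SD and about 24% at the upper end of the assumed laboratory range. If performance is eligible and enters when significant, rejection stays near 5-6%. For injury history in the field, a moderate split (12/20 vs 8/20 to 14/20 vs 6/20) gives a false difference of 0.10-0.40 SD and 5.4-17.4% rejection, if injury history shifts gait by 0.5-1.0 SD.

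The change is worth making because it is cheap and serves the Discussion's stated aim. The laboratory validity and reliability results are not affected.

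**What to change.** In Statistical analysis (Exploratory clinical validation analysis):

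1. Add injury history (yes/no, as defined in Data collection) as a prespecified covariate in the field performance-level ANCOVA.
2. Add age-graded 5 km performance (continuous) as a prespecified covariate in the laboratory injury-history ANCOVA.
3. Include both whatever their p-values.
4. Tabulate the other factor by group for each contrast.
5. Report each contrast with and without the added covariate, since part of the association may run through it.

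The cost is a sentence or two of text, one degree of freedom per model and a second estimate to report. No new data are needed. Some precision is lost when the factors overlap: variance inflation is about 1.04-1.19 for moderate imbalance and 1.56 at 16/20 vs 4/20. This is offset where the covariate explains gait.

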### Exploratory clinical validation aims

Explore differences in running gait outcomes within different clinical (injured vs non-injured) and performance (elite vs novice) groups.Explore relationships between real-world running gait and demographic characteristics (e.g., sex, age) in different clinical and performance groups (e.g., those with a previous injury or different performance level).Investigate the usability of the wearable devices in adult runners.

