## Materials and methods

### Study design

This is a cross-sectional study that will assess the validity and reliability of three grades of wearables (research, entry-level commercial and advanced / novel multimodal). The protocol was developed according to the Standard Protocol Items: Recommendations for Interventional Trials’ (SPIRIT) checklist [24], as appropriate (see S1 File). As this is a study protocol, no data has been included and conforms to PLOS data policy. The overall schedule and time commitment for trial participants are depicted in Fig 1 and S1 File.

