#### Real-World environment testing

Data from the novel multimodal, commercial, and research-grade wearables will be collected within real-world environments to test the clinical / performance validity of the wearables (i.e., can they differentiate or provide meaningful data on relevant populations). Recruitment for the real-world environment testing began in June 2023 with an expected end date October 2023.

*Participants*. Within the real-world environment testing 40 individuals, specifically novice/amateur (n = 20) and expert/sub-elite (n = 20) running performance level. Performance level will be based on their 5km running time (i.e., age graded performance % [35]).

*Wearable location*. Each participant will be equipped with the DANU Sports System (socks on both feet), two Axivity AX6 sensors attached to the shoelaces and two DorsaVi ViMove2 sensors on the tibia.

*Running procedures*. All participants, regardless of performance level, will be asked to complete a 5km run on a standardised route in North-East England. The course will be run on a mixture of trail paths and concrete paths, with 174ft elevation gain throughout. Information about conditions (e.g., environment and shoes) and objective load data (e.g., time and pace) will be collected. Participants will wear their own running shoes.

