#### System usability scale

Upon immediate completion of the real-world environment testing, participants will be asked to complete the System Usability Scale (SUS) to assess the usability of each of the wearables. The SUS is a simple scale based, multiple-choice questionnaire proposed by John Brooke in 1986 and has been widely adopted in product usability evaluations [36–38]. A final score is provided with interpretation based on a well-established reference standard, with an excellent reliability (0.85) [39]. Overall, the SUS is a quick and simple method for usability evaluation.

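### SUS correlations with price, weight and battery life rest on three devices and cannot support inference, and no planned test compares SUS between the devices

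*Protocol article*

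**What the plan says.** All references are to the protocol article.

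- **Aim.** Under Exploratory clinical validation aims, the usability aim is to "Investigate the usability of the wearable devices in adult runners". The Outcome measures section makes usability a secondary outcome.
- **Devices.** The Study design section says "This is a cross-sectional study that will assess the validity and reliability of three grades of wearables". The Wearables section names one product per grade: Axivity AX6, DorsaVi ViMove2 and DANU.
- **Who rates what.** SUS is collected after the real-world run, where "participants will be asked to complete the System Usability Scale (SUS) to assess the usability of each of the wearables". In that arm, "Each participant will be equipped with the DANU Sports System (socks on both feet), two Axivity AX6 sensors attached to the shoelaces", together with the two DorsaVi sensors. The arm has 40 runners, "specifically novice/amateur (n = 20) and expert/sub-elite (n = 20) running performance level".
- **Analysis.** The usability paragraph of the Statistical analysis section plans three things:
  1. SUS scores for each wearable, computed and plotted.
  2. Separate ANOVAs, described as "The ANOVAs will determine the differences between the SUS scores within the different device grades between participant groups", with injury history and performance level as examples of the groups.
  3. Pearson correlations of SUS with demographics and with device characteristics: "wearables characteristics (e.g., price, weight, and battery life) will be explored using Pearson correlations". Correlations are graded small below 0.30, medium from 0.30 to 0.50 and strong above 0.50.
- **Significance.** The level is p < 0.05, without control for multiple comparisons.

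**The concern.** Price, weight and battery life belong to the device, not to the runner. With one product per grade there are three price values, three weights and three battery lives, however many runners are recruited. A correlation with such a trait is therefore a statement about three points. A larger sample makes each device's mean SUS more precise but adds no device. The study could report that usability rises or falls with price or weight when the data cannot tell price from weight, or either from fit, placement, software or any other way in which the three products differ.

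The second part concerns the ANOVAs. All 40 real-world runners wear and rate all three systems, so the design provides paired device comparisons. The factor in the stated ANOVAs is participant group, examined one device at a time. The pairing is not used, and any statement that one device is rated as more usable than another would rest on inspection of a plot.

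**Working it through.** **Inputs from the protocol:** 3 devices; 40 real-world runners (20 + 20), each rating all three; p < 0.05; r > 0.50 labelled strong. Two-sided testing is assumed. The protocol gives no SUS standard deviation, effect size or within-runner correlation, so those below are assumptions shown as ranges. The usability sample-size rationale rests on the share of use issues found with 15–20 people per group. It has no SUS quantity behind it, so there is no planned figure to reproduce.

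**Step 1: what the data can identify.** Three device means leave 3 − 1 = 2 degrees of freedom between devices. Three characteristics plus everything else that differs between the products cannot be separated on 2 degrees of freedom.

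**Step 2: the possible readings of the correlation.** The critical value is |r| = t / √(t² + n − 2), where t is the two-sided 5% point on n − 2 degrees of freedom.

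- *Device means, n = 3.* t = 12.706 on 1 df, so |r| = 12.706 / √(161.45 + 1) = 0.997. With no relation and normal errors, r for three points behaves as the cosine of a uniformly distributed angle, so P(|r| > 0.50) = 2/3; simulation gave 66.7%. The usual Fisher interval does not exist, because its standard error is 1/√(n − 3) = 1/√0. Significance is almost unattainable, yet the protocol's scale calls pure noise strong two times in three.
- *All ratings pooled, n = 120.* t = 1.980 on 118 df, so |r| = 1.980 / √(3.92 + 118) = 0.179. The 40 ratings of one device share one trait value and are not 40 independent pieces of evidence about that trait.
- *Within one device.* The trait is constant and r is undefined.

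**Step 3: false positives under pooling.** Simulated: 40 runners × 3 devices, no effect of the trait, devices differing for unrelated reasons, naive Pearson test on 120 rows.

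| Assumed device SD | Other assumptions | Rejection rate |
|---|---|---|
| 0 | within-runner correlation 0 | about 5% |
| 0 | within-runner correlation 0.3 to 0.5 | 0.5% to 2.5% |
| 3 SUS points | runner SD 10, residual SD 15 | 14% |
| 5 SUS points | same | about 30% |
| 8 SUS points | same | 49% |
| 0.2 SUS SD | within-runner correlation 0 to 0.5 | 18% to 22% |
| 0.3 SUS SD | same | 32% to 36% |
| 0.5 SUS SD | same | 52% to 55% |

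The reason is visible by hand. At within-runner correlation 0.3, the within-runner part of a device mean has standard error √(0.7/40) = 0.13 SD. A real device difference of 0.3 SD is more than twice that, and the pooled test credits it to whichever trait happens to line up.

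**Step 4: what a paired device comparison would offer.** For a pairwise difference d (in SUS SDs) and within-runner correlation ρ, the standardised paired difference is d / √(2(1 − ρ)), with 39 df. For d = 0.5, unadjusted two-sided 5%:

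- Power is 59%, 74% and 87% at ρ = 0, 0.3 and 0.5.
- 80% power needs a standardised paired difference of 0.454. That is d = 0.454 × √2 = 0.64 at ρ = 0, 0.54 at ρ = 0.3 and 0.45 at ρ = 0.5. The runner and residual SDs used in Step 3 imply ρ = 100/325 = 0.31, hence about 0.53.

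The planned 20 v 20 group comparison within one device has 34% power for a group difference of 0.5 SD and needs about 0.91 SD for 80%. It answers a different question, so this is no like-for-like contrast. It shows only that the stated tests use the less informative side of the design.

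**The case against.** The best defence is that this is a pilot, usability is a secondary outcome listed last among exploratory aims, and that aim states no device-versus-device hypothesis. SUS will be computed and plotted for each wearable, and the System usability scale section provides for interpretation against a reference standard. The ANOVAs have a coherent purpose of their own: group differences within each grade. The protocol never says that 120 rows will be pooled, and every SUS variance used above is assumed.

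Much of this stands, and it rules out several stronger readings.

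- A reader might infer that the plan cannot answer its usability aim. It can, descriptively, through the SUS scores per wearable.
- A reader might infer that any significant link with price or weight would be an artefact. The rate depends on pooling and on how much devices differ for other reasons; with no device differences it is at or below 5%.
- A reader might extend the criticism to all the SUS correlations. Those with demographics, run within each device, have up to 40 independent runners and are unaffected.
- A reader might cite the Discussion sentence "This study will determine what grade of wearable may be necessary to provide meaningful data on real-world running" as a usability claim. It concerns running data, in the clinical validation part, and says nothing about SUS.
- The order of the three SUS forms is not described, but that is a detail an article commonly leaves out and is no finding.

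The exploratory label does not rescue the trait correlations: none of the readings in Step 2 yields a usable result, and more runners would not change that. Nor does it explain leaving the paired ratings without a device comparison when the Discussion expects to learn about acceptance of the three systems.

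**Conclusion.** The point holds in two parts. First, the Pearson correlations of SUS with price, weight and battery life cannot support inference with three devices. This follows from the number of devices alone. The 0.997 and 0.179 thresholds follow from n and two-sided 5% testing, and the 67% from n = 3 with normal errors. The 14% to 55% false-positive range additionally assumes pooling and the device SDs shown.

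Second, the SUS ANOVAs as described compare participant groups within a device grade, so no inferential analysis compares devices. The sentence introducing them is ambiguous, but the sentence defining them is not.

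Severity is moderate. The primary validity and reliability analyses are untouched, the aim is otherwise met descriptively, and the paired SUS data will be collected anyway, so nothing is lost if the analysis is changed.

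**What to change.** - Remove the correlations of SUS with price, weight and battery life. Show these characteristics in a descriptive table beside each device's SUS summary. Keep the SUS–demographic correlations, run within each device.
- Add one repeated-measures or mixed model of SUS, with device within runner and performance level between runners. Performance level is the grouping whose sizes are fixed in the arm that completes the SUS. With 40 complete runners, the device test has 2 and 2 × (40 − 2) = 76 degrees of freedom (2 and 78 without the group factor). Report the three paired device differences with 95% CIs.
- Word usability conclusions as applying to these three devices.

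The cost is a little analysis work and a few sentences of protocol text. No new data are needed. The study gives up inference on which device characteristics go with usability, which three devices could not provide.
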